#### 643 Health economic outcome measures

644

645 For the primary cost-effectiveness analysis, the primary outcome will be QALYs, derived  
646 from the EQ-5D-5L outcome measure. The EQ-5D-5L is a generic, preference based,  
647 health-related quality of life (HRQoL) measure. It consists of two parts, a five  
648 item questionnaire and a visual analogue scale (EQ-VAS). The EQ-5D-5L questionnaire is  
649 scored between 0 and 1, with 1 meaning full HRQoL and 0 death (some scores may fall  
650 below 0). Each set of answers on the EQ-5D-5L is assigned a utility score between 0 and 1  
651 based on general population weighting of health states. This measure can then be used to  
652 generate QALY estimates by assigning a quality of life weight to the length of time a person  
653 is in a given health state.

654

655 Secondary cost-effectiveness analyses will be conducted using the Bangor Goal Setting  
656 Interview and HADs outcome measures. These will be used to develop incremental cost-  
657 effectiveness ratios (ICERs) to express cost-effectiveness in natural units of effect, which will  
658 in turn allow comparison with the QALY outcomes. Comparing these outcomes will help to  
659 determine relative agreement between the generic QALY outcomes and 23 clinically relevant  
660 outcomes.

661

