#### 662 Health economic data collection

663

664 In order to collect data on the cost of the interventions, health service use and wider  
665 costs/benefits to society, we will record study participant primary and secondary care health  
666 and social care service use over the follow-up period using a client service receipt inventory  
667 (CSRI) to collect service use data from participants, and further triangulated with linked  
668 routinely collected data. We will make use of national unit costs and routine hospital  
669 data/manufacturers data to cost the intervention and service use. We will also consider the  
670 financial implications of presenteeism and absenteeism by calculating the number of  
671 participant workdays lost during the follow-up period and triangulating with income data.

672

673 Health economic data analysis

674

675 We will conduct an economic evaluation at the end of the 3-month follow-up period, based  
676 on the following components:

- 677     • Conduct a primary cost-utility analysis using the EQ-5D-5L as the measure of utility  
678     to generate a cost per QALY estimate.
- 679     • Conduct a secondary cost-effectiveness analysis using the relevant trial outcomes  
680     (Bangor Goal Setting interview, HADs), and develop incremental cost-effectiveness  
681     ratios (ICERs) to express cost-effectiveness.
- 682     • For all analyses, we will use bootstrapping to produce cost-effectiveness  
683     acceptability curves for comparison with the NICE ceiling of £20,000 to £30,000 per  
684     QALY in the UK to communicate to policymakers the probability that the  
685     intervention is cost-effective.
- 686     • Conduct sensitivity analyses to investigate uncertainty in the data.

687 The incremental costs and consequences of the treatment arms will be compared and  
688 expressed in cost per QALYs where possible. We will use a UK tariff as a source of EQ-5D-  
689 5L values for the cost-utility analysis and compare values to UK population norms. In the  
690 event that neither intervention is found to have a significant effect on patient outcomes, we  
691 will be unable to perform a robust analysis of cost-effectiveness. We will therefore present a  
692 cost-consequence analysis, whereby the costs and effect data are presented in a  
693 disaggregated manner. Additional cost-effectiveness analyses using the secondary  
694 outcomes will be carried out for comparative purposes

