### **4.2 RANDOMISATION**

Randomisation will take place once consent and baseline data collection has been completed. Randomisation will be on a 1:1 allocation (intervention:control) via a secure online system hosted by NWOORTH, Bangor University. The system will employ a dynamic adaptive randomisation algorithm. The randomisation will be stratified for centre (London/Sussex/Southampton/Manchester). A member of the research team at UCL will enter the participants details into the web form and perform the randomisation, which will either display directly on screen, if the researcher is unblinded or notification of the randomisation result will be sent to the designated parties to organise ongoing contact.

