### **5.2 TIME POINTS OF OUTCOMES MEASURES**

Outcome measures are collected at baseline, 3 months and 6 months post-randomisation. Appendix 1 contains a list of all data collected during the study.

The primary outcome is participant-reported goal attainment at 3 months post-randomisation. This will also be collected as a secondary outcome at the 6 month post-randomisation follow up. This will be collected using the Bangor Goal Setting Interview (BGSi).

Secondary outcomes will be:

- Goal Satisfaction Scale ((using the Bangor Goal Setting Interview Scale)
- Cognitive function (tested using the cognitive batteries employed for Workstream 1)
- Quality of life (EQ-5D-5L)\*
- Life Space Assessment
- Social Functioning (SF-DEM)
- Instrumental Activities of Daily Living (IADL) Scale
- Generalised Anxiety Disorder Assessment (GAD-7)
- Patient Health Questionnaire (PHQ-8)
- Chalder Fatigue Scale
- Pittsburgh Sleep Quality (PSQI)
- DePaul Symptom Questionnaire – Post-Exertional Malaise (DSQ-PEM).
- Client Service Receipt Inventory (CSRI)\*

Cognitive function will be assessed using three complementary assessments (expanded below), to maximise understanding of cognition

- Cognitive function assessment 1 – battery of Cognitive tests
  - The Repeatable Battery for the Assessment of Neuropsychological Tests (RBANS)
  - The Delis-Kaplan Executive Function System: The Trail Making Test (Condition 2: Number Sequencing & Condition 4: Number-Letter Switching)
  - The Delis-Kaplan Executive Function System: Colour-Word Interference
  - The Delis-Kaplan Executive Function System: Phonemic Fluency
  - Wechsler Adult Intelligence Scale III: Digit Span
  - Test of Premorbid Functioning (TOPF)
- Cognitive function assessment 2 – online battery of cognitive tests
  - Gorilla
  - 4 Mountains (4MT)
- Cognitive function assessment 3
  - Neotiv suite

\*Health economic data not being analysed at by NWO.

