## 6.6 ANALYSIS OF PRIMARY OUTCOME

The primary outcome, the BGSi (attainment score) at the 3 months, will be analysed using a multi-level (mixed effect) linear regression model to assess the differences between the two treatment arms. Stratification variables (Site) will be incorporated into the model as a random effect along with gender, age (continuous), years of education (continuous) and RBANS composite score at baseline as fixed factors. Baseline BGSi attainment score will also be incorporated to account for any differences at baseline.

The BGSi at 6 months will be analysed as a secondary outcome using the same model structure as the primary. Unadjusted (section 6.5) and adjusted results will be presented with associated 95% confidence intervals.

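### The protocol does not say how QALYs are built from baseline and follow-up utility, and states no adjustment of incremental QALYs for baseline EQ-5D-5L utility

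*Combined protocol and SAP*

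**What the plan says.** **QALY definition.** Protocol 5.2.2.4 (Health economic outcome measures) makes QALYs from the EQ-5D-5L the primary economic outcome. The measure is used to "generate QALY estimates by assigning a quality of life weight to the length of time a person" spends in a health state. No integration rule or measurement points are named.

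**Horizon and comparison.** The same section (Health economic data analysis) says "We will conduct an economic evaluation at the end of the 3-month follow-up period, based" on a cost-utility analysis and supporting analyses. It then says "The incremental costs and consequences of the treatment arms will be compared and" given as cost per QALY where possible. On uncertainty: "For all analyses, we will use bootstrapping to produce cost-effectiveness" acceptability curves, "for comparison with the NICE ceiling of £20,000 to £30,000 per" QALY. No regression model, covariate or baseline term appears.

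**Timing.** SAP 5.2: "Outcome measures are collected at baseline, 3 months and 6 months post-randomisation". SAP 4.2: "Randomisation will take place once consent and baseline data collection has been completed". The only utilities inside a 3-month horizon are therefore the pre-randomisation value and the 3-month value.

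**Clinical outcomes.** SAP 6.6 on the primary outcome: "Baseline BGSi attainment score will also be incorporated to account for any differences at baseline". SAP 6.7 does the same for the secondary outcomes that the SAP models. The SAP places health economics outside its scope (footnote to the aims in 3.2) and marks EQ-5D-5L as health economic data in 5.2 and Appendix 1.

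**The concern.** A QALY that integrates utility from baseline contains a component that treatment cannot have affected. Suppose two participants both reach 0.70 at 3 months, one from 0.50 and the other from 0.60. By the trapezium rule they score 0.25 × (0.50 + 0.70)/2 = 0.1500 and 0.25 × (0.60 + 0.70)/2 = 0.1625. The gap of 0.0125 is pre-treatment health.

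Across arms, a chance difference in baseline utility passes into the incremental QALY in the same way. Bootstrapping displays that variation but does not remove it. The trial is sized for the BGSI alone and no precision is stated for QALYs, so avoidable noise in the primary economic outcome deserves attention. Leaving both the construction and the adjustment open also allows the choice to be made after the ratio has been seen against the threshold.

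**Working it through.** **1. The plan's own figure.** Protocol power calculation and SAP 4.1: effect 0.7 SD, 90% power, two-sided 5%. The two-sample t-test gives 43.87, so 44 per arm (88 in total, power 0.901). Allowing for 25% attrition, 88/0.75 = 117.3, so 118. The stated numbers reproduce. I use 44 per arm below.

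**2. Assumptions.** The documents give neither the SD of utility (s) nor the baseline to follow-up correlation (r). I take s = 0.20 to 0.30 and r = 0.3 to 0.8, with equal SDs at each time and, for 6 months, the same correlation between all pairs of times.

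**3. Size of chance imbalance.** The SE of the baseline difference is s × √(2/44) = 0.213s, which is 0.043 at s = 0.20 and 0.064 at s = 0.30. A difference above 0.05 in either direction then arises in 24% to 43% of trials. Through the baseline half of the area alone, it moves the QALY difference by 0.125 × 0.05 = 0.00625.

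**4. Variance with and without adjustment (multiples of s², common scale factors omitted).**
- 3-month trapezium, QALY = 0.125(u0 + u3): unadjusted 2 + 2r; adjusted 1 − r²; ratio (1 − r)/2. At least half the variance is removable for any r of 0 or more.
- 6-month trapezium, weights 0.5, 1, 0.5: unadjusted 1.5 + 2.5r; adjusted 1.25 + r − 2.25r².
- 3-month utility applied to the whole period: unadjusted 1; adjusted 1 − r².

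These ratios do not depend on s or n. They ignore the small cost in degrees of freedom.

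| r | 3-month trapezium: variance removed (SE cut) | 6-month trapezium | 3-month utility only |
|---|---|---|---|
| 0.3 | 65% (41%) | 40% (23%) | 9% (5%) |
| 0.4 | 70% (45%) | 48% (28%) | 16% (8%) |
| 0.6 | 80% (55%) | 65% (41%) | 36% (20%) |
| 0.8 | 90% (68%) | 83% (58%) | 64% (40%) |

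**5. Simulation of the 3-month trapezium.** 20,000 trials, 44 per arm, s = 0.25, r = 0.6, and an illustrative true utility gain of 0.05 at 3 months (0.00625 QALY). Both estimators average 0.0062 to 0.0063, so neither is biased. The SD is 0.0119 unadjusted and 0.0054 adjusted. The estimated QALY difference has the wrong sign in 30% and 12% of trials respectively.

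**6. Carry-over to net benefit.** Take s = 0.25 and r = 0.5. The SE of the QALY difference is 0.01154 unadjusted and 0.00577 adjusted, worth £231 and £115 per patient at £20,000 per QALY. Now add costs independent of QALYs, with an assumed SD of £1,000 or £3,000 (SE of the difference £213 or £640):
- £1,000: √(231² + 213²) = £314 falls to √(115² + 213²) = £242, a cut of 23%.
- £3,000: £680 falls to £650, a cut of 4%.
- At £30,000 per QALY the cuts are about 32% and 9%.

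**The case against.** **Silence is not a decision.** The protocol does not rule adjustment out, and an arm comparison can be an adjusted one. The economic analysis is done outside the SAP, and any separate plan for it is not among the documents. Protocol section 6 also has secondary outcomes, EQ-5D-5L among them, use the primary model when that can be done. This stands against any claim that the plan has chosen an unadjusted comparison. It does not fill the gap: section 6 names stratification variables and factors still to be chosen, but no baseline score, and it is not applied to QALYs.

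**The area under the curve is inferred.** This is correct; the text gives only weight times time. The size of the gain depends on the construction, and with the 3-month utility alone it is modest at low correlations. Adjustment helps under each of the three constructions considered.

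**Randomisation protects the comparison.** On average it does, and the bootstrap reflects the extra variance. A reader might infer that the unadjusted ratio is biased or invalid; it is not. The loss is precision, and exposure to chance imbalance in this one trial.

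**Cost per QALY also carries cost variance.** A reader might transfer the 45% to 68% to the cost-per-QALY answer or the acceptability curve. Step 6 shows why that fails: the gain there can be far smaller, and the documents give no cost SD.

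**The treatment effect is unknown.** A reader might also conclude that baseline imbalance is as large as the benefit. The documents give no expected EQ-5D-5L effect, so the 0.05 is only an illustration.

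**Conclusion.** The point holds as a gap in specification with a better method readily available. No part of the protocol or SAP states how QALYs are constructed or that incremental QALYs will be adjusted for baseline utility, although the SAP adjusts the clinical outcomes it models in this way.

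If the trapezium rule is used over the stated 3-month horizon, adjustment cuts the SE of the QALY difference by 45% to 68% for r of 0.4 to 0.8; over 6 months the cut is 28% to 58%. If only the 3-month utility is used, 9% to 64% of the variance is removed for r of 0.3 to 0.8. All of these rest on assumed correlations and equal SDs, and they apply to the QALY difference only. The reduction for net benefit or cost per QALY is smaller, by an amount that depends on cost variance the documents do not give. The sponsor should make the change, but the plan as written is incomplete rather than invalid.

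**What to change.** In protocol 5.2.2.4, or in a health economics analysis plan fixed before economic data are seen by arm, state:

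1. How each participant's QALY is built: the integration rule, the utility time points used and the horizon.
2. That incremental QALYs are estimated by regressing QALY on allocation, baseline EQ-5D-5L utility and site.
3. That this model is refitted together with the cost model in every bootstrap replicate used for the ICER, the cost-effectiveness plane and the acceptability curve. Unadjusted results may be reported alongside.

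The cost is a few sentences and one covariate that is already collected. A participant without baseline utility would need it imputed, but a QALY that integrates from baseline needs that value in any case.

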### 3 Research questions and objectives

This proposal comprises two workstreams. Workstream 1 aims to phenotype cognitive Covid-19, while Workstream 2 will develop and test the effectiveness of a neuropsychological rehabilitation intervention to support recovery from cognitive Covid

#### 3.1 Research questions Workstream 1

- What is the phenotype of 'cognitive' Covid?
  - What aspects of cognition are primarily affected in cognitive Covid and what is the range of severity?
- What is the inter-relationship between cognitive impairment and other core features of long Covid, ie fatigue, sleep disturbance, anxiety and depression?
- What are the MRI correlates of cognitive Covid, measured in terms of brain structure and connectivity?
- What is the effect of the CV19 vaccine on cognitive symptomatology?
- Does cognitive impairment in long Covid correlate with molecular markers of inflammation or neurodegeneration?

#### 3.2 Research questions Workstream 2

- Can neuropsychological rehabilitation improve the cognitive and functional outcomes of people with cognitive Covid?
- What is the incremental cost-effectiveness of CIVIC-Rehab compared to standard clinical care for cognitive Covid?
- What is the cost per quality-adjusted life year (QALY) of CIVIC-Rehab compared to standard clinical care for cognitive Covid, and does this fall below the NICE threshold of £20,000 to £30,000 per QALY?

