#### 5.2.2.1 Trial design

This will be an individually randomised parallel group controlled trial, comparing the study intervention (cognitive rehabilitation) with the clinical standard of care (current clinical management pathways for long Covid, including treatment for fatigue, respiratory disorders, sleep, anxiety and depression).

590

591 5.2.2.2 Participant flow

592

593 Post-consent participants will undergo baseline assessment before randomisation to receive  
594 either neuropsychological rehabilitation or treatment as usual.

595

596 5.2.2.3 Outcome measures

597

598 The primary outcome will be participant-reported goal attainment at 3 months post-  
599 randomisation. This will also be collected at the 6 month post-randomisation follow up. This  
600 will be collected using the Bangor Goal Setting Interview (BGSi).

601

602 Secondary outcomes will be:

- 603 • Cognitive function (tested using the cognitive batteries employed for Workstream 1)
- 604 • Quality of life (EQ-5D-5L)
- 605 • Life Space Assessment
- 606 • Social Functioning (SF-DEM)
- 607 • Instrumental Activities of Daily Living (IADL) Scale
- 608 • Generalised Anxiety Disorder Assessment (GAD-7)
- 609 • Patient Health Questionnaire (PHQ-8)
- 610 • Chalder Fatigue Scale
- 611 • Pittsburgh Sleep Quality (PSQI)
- 612 • DePaul Symptom Questionnaire – Post-Exertional Malaise (DSQ-PEM).
- 613 • Client Service Receipt Inventory (CSRI)

614

615 5.2.2.4 Health economic analyses

616

617 From a public sector, multi-agency perspective we will conduct an economic evaluation to  
618 determine the incremental cost-effectiveness of the intervention in comparison to clinical  
619 standard of care. The intervention of interest will be a novel neuropsychological rehabilitation  
620 intervention programme for cognitive Covid compared to clinical standard of care (i.e. current  
621 clinical management pathways for long Covid, including treatment for fatigue, respiratory  
622 disorders, sleep, anxiety and depression). We will examine two research questions during  
623 the economic evaluation:

624

- 625 1. What is the incremental cost-effectiveness of CICERO-Rehab compared to standard  
626 clinical care for cognitive Covid?
- 627 2. What is the cost per QALY of CICERO-Rehab compared to standard clinical care for  
628 cognitive Covid, and does this fall below the NICE threshold of £20,000 to £30,000  
629 per QALY?

630

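### The planned cost-per-QALY analysis gives way to a cost-consequence analysis whenever an unnamed significance test fails, although the cost-per-QALY question is asked without condition

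*Combined protocol and SAP*

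**What the plan says.** Protocol 3.2 asks, as the third Workstream 2 question, for the cost per QALY and "does this fall below the NICE threshold of £20,000 to £30,000 per QALY". Section 5.2.2.4 repeats it as the second of two economic questions: "What is the cost per QALY of CICERO-Rehab compared to standard clinical care for" cognitive Covid. Neither place attaches a condition.

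Under the outcome measures in 5.2.2.4: "For the primary cost-effectiveness analysis, the primary outcome will be QALYs, derived" from the EQ-5D-5L. Under data analysis in the same section, a primary cost-utility analysis is listed, and "For all analyses, we will use bootstrapping to produce cost-effectiveness" acceptability curves, to be compared with the NICE range. The section goes on to plan deterministic and probabilistic sensitivity analysis.

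Between these two plans stands the rule at issue. Should it turn out that "neither intervention is found to have a significant effect on patient outcomes", the team "will be unable to perform a robust analysis of cost-effectiveness. We will therefore present a" "cost-consequence analysis, whereby the costs and effect data are presented in a" disaggregated form. The paragraph closes by keeping some further work: "Additional cost-effectiveness analyses using the secondary" outcomes, for comparison.

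The SAP does not alter this. The footnote to its aims places health economics outside its scope, and SAP 5.2 marks the EQ-5D-5L and CSRI as not analysed there.

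**The concern.** The rule makes the main economic analysis depend on a significance test. Cost-effectiveness is a joint statement about incremental costs and incremental effects. A non-significant effect is an imprecise estimate; it is neither evidence of no effect nor an obstacle to estimating the joint distribution.

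The test is also not identified. The text does not say whether the relevant outcome is the BGSI, the EQ-5D-5L, or any or all of the outcomes, nor whether it is judged at 3 or 6 months. It speaks of neither intervention, although the trial compares one intervention with standard care. The decision to run the cost-utility analysis could therefore be settled after results are known.

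Two things are at stake. A stated research question may go unanswered, since a table of separate costs and effects yields no cost per QALY. And if the gate is the EQ-5D-5L, a cost per QALY that is published only after a significant result will tend to look too favourable.

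**Working it through.** **Inputs from the documents.** Design effect 0.7 SD on the BGSI at 3 months, 90% power, 5% level, 44 evaluable per arm, 25% attrition, 118 randomised (Protocol power calculation; SAP 4.1); two-sided tests (SAP 4.3). **Assumed, because the documents give no figure:** true effects other than 0.7 and 0.8 SD, including any EQ-5D-5L effect; a baseline-to-follow-up correlation of 0.5; and 10 outcomes with pairwise correlation 0.5.

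**1. Reproduce the plan's figure.** Normal approximation: n per arm = 2(1.960 + 1.282)² / 0.7² = 21.02 / 0.49 = 42.9. The two-sample t-test gives 43.87, so 44 per arm and 88 in total. 88 / 0.75 = 117.3, so 118 (59:59). The plan's figures reproduce.

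**2. Chance that one outcome is non-significant despite a real effect.** This is 1 − power of the two-sample t-test, two-sided 5%, unadjusted:

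| True effect (SD) | 44 per arm | 59 per arm (no attrition) |
|---|---|---|
| 0.8 | 4% | 1% |
| 0.7 (design) | 10% | 3.5% |
| 0.5 | 36% | 23% |
| 0.4 | 54% | 42% |
| 0.3 | 71% | 63% |
| 0.2 | 85% | 81% |

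At 44 per arm, an observed difference below about 1.96 × √(2/44) = 0.42 SD is non-significant.

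**3. Baseline adjustment.** With correlation 0.5 the residual variance falls by the factor 1 − 0.5² = 0.75, so the effective effect is d / √0.75. At 44 per arm the chance becomes 3.7% at d = 0.7 (effective 0.808), 24% at 0.5, 64% at 0.3 and 81% at 0.2.

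**4. If every outcome must be non-significant.** Let δ = d√(44/2) = 4.69d be the mean of each test statistic. The chance that all 10 equicorrelated statistics lie within ±1.96 is about 46% at d = 0.2, 25% at 0.3, 3.5% at 0.5 and 0.1% at 0.7, taking the same true effect on all 10.

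**5. Selection.** Among results significant in favour of rehabilitation, the mean estimate divided by the true effect is [δ + φ(1.96 − δ) / (1 − Φ(1.96 − δ))] / δ. For d = 0.7, δ = 3.28 and the ratio is 1.06. It is 1.24 at d = 0.5, 1.8 at 0.3 and 2.6 at 0.2. If the gate is the EQ-5D-5L and QALY gains follow it, the denominator of the published cost per QALY is inflated by about these factors.

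**6. The provisions side by side.** The question is unconditional; the acceptability curves are promised for all analyses; the probabilistic sensitivity analysis is planned without a condition. Each of these describes an uncertain effect. The rule withdraws the analysis in the situation where they are most needed.

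**The case against.** The best statistical defence is that a ratio with a near-zero denominator is unstable, so an ICER after a null result may mean little. That is true of the ratio. It is not true of the cost-effectiveness plane or the acceptability curve, which need no ratio and are already planned.

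Several textual objections carry weight. The fallback is pre-specified and disclosed, and costs and effects would still be published. A general statement about bootstrapping followed by a named exception is poor drafting but need not be a contradiction. The plural in the trigger may well mean that all outcomes must be non-significant, which makes the rule fire less often (step 4). The figures in step 2 ignore covariate adjustment, which lowers them (step 3), although the SAP models do not cover the EQ-5D-5L. The closing sentence about secondary outcomes could, read literally, rescue a QALY analysis, because the EQ-5D-5L is a secondary trial outcome. But QALYs are the primary economic outcome, so it is unclear whether that sentence reaches them once the rule has fired.

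The primary endpoint, the sample size and data collection are untouched. These points limit the frequency and severity. None explains why a p-value should decide whether the cost-per-QALY question is answered.

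**Conclusion.** The point holds as a should-fix. The protocol gates its primary cost-utility analysis on an unspecified significance test, while asking the cost-per-QALY question unconditionally and already planning the methods that handle an uncertain effect.

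The size cannot be fixed while the trigger is undefined. On the BGSI at the protocol's own effect of 0.7, about 1 trial in 10 with a real effect would lose the analysis (44 per arm, unadjusted). On a single outcome with an assumed true effect of 0.5 to 0.2 SD, 36% to 85% would. Both figures fall under baseline adjustment or an all-outcomes reading.

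A reader might infer more than this. One inference is that the economic evaluation is dropped altogether; the text substitutes a cost-consequence analysis and may retain further cost-effectiveness work. Another is that the analysis would be lost in many trials with a real effect; that is not so at the design effect, and becomes so only under smaller effects that the documents do not state. A third is that published cost-effectiveness would be badly biased in any case; if the gate is the BGSI at its design power, the overstatement of the BGSI effect is only about 1.06-fold. The documents support none of these stronger readings.

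**What to change.** Delete the significance condition from Protocol 5.2.2.4. State instead that incremental costs, incremental QALYs, the bootstrapped cost-effectiveness plane and the acceptability curve, read at £20,000 and £30,000 per QALY, will be reported whatever the statistical significance of the clinical outcomes. Keep the cost-consequence table as a supplement. Where the QALY difference is close to zero, say that the ICER is unstable and rely on the plane and curve. Net monetary benefit would be a convenient addition but is optional. Clarify whether the additional analyses on secondary outcomes include QALYs.

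The cost is a wording change in the protocol or a health economics analysis plan. The EQ-5D-5L and CSRI are already collected, and neither the sample size nor the burden on participants changes. The change should be made and dated before the economic results are seen by arm.
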